### Environmental exposure assessments

The study will involve the measurements of indoor criteria air pollutants, mold, and environmental conditions, including temperature and relative humidity (T/RH) to assess the magnitude of exposures in homes. Research-grade air quality sensors will be deployed for approximately one week during the four scheduled visits (V1–V4). The TSI Q-Trak XP IAQ monitor (7585) and DustTrak aerosol monitor (8530) will be placed alongside the indoor low-cost sensors to provide accurate measurements of size-resolved PM, NO_2_, NO, CO, O_3_, and formaldehyde (HCHO).

Additionally, low-cost sensors will continuously collect indoor and outdoor air quality data over the two-year study period. A total of 160 sensors will be fabricated using a microcontroller (Raspberry Pi 4 Model B, 4 GB) and multiple pollutant sensors, including a Sensirion SPS30 for PM, an Adafruit SGP30 for VOCs, an Amphenol MiCS-2714 for NO_2_, and a Sensirion SCD4x for CO_2_ and T/RH, with an estimated cost of approximately $150 per unit. Those economically viable sensor selections are verified in a similar study to measure indoor environmental quality for residential buildings [37]. The low-cost air quality sensors will be deployed indoors (primarily in the living room) and outdoors (primarily in the backyard or porch area) during the first follow-up visit (V1) and will remain in place throughout the study. For each visit, the research team will log the senor readings to check the quality of data collection with proper tech maintenance on the sensors. Long-term time-series data from these sensors will be calibrated against short-term (approximately 1-week) high-accuracy measurements measured by research-grade instruments, and additional details on the calibration process are provided in the Statistical Analysis Plan section.

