Moreover, the study will involve mold assessments through spore-trap analysis of air samples, direct microscopic examination of surface samples, and fungal DNA sequencing of dust samples. Indoor and outdoor air samples will be collected using an Air-O-Cell sampling cassette with a calibrated Bio-Pump (Environmental Express), surface samples with sterile cotton-tipped swabs, and dust samples from HVAC filters and/or damp areas with visible mold or water damage (e.g., kitchen and bathroom) in each home at V1 and V4. Air and surface samples will be submitted to the accredited laboratory Eurofins USA for spore-trap and direct microscopic analyses. The dust samples will be sent to Co-PI [name]’s lab for storage, DNA extraction, followed by fungal Internal Transcribed Spacer (ITS) sequencing at the North Texas Genome Center at UTA within three months of sample collection completion.

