### Power calculations

The sample size and statistical power for this 4-arm parallel-group randomized controlled trial is analyzed for various scenarios based on a range of likely magnitudes of outcomes for asthma-related health outcome and environmental exposure assessments (Table 1). Calculations are made utilizing a robust statistical software tool, G*Power ver. 3.1.9.7, for a repeated measures ANOVA with a within-between interaction [49]. A range of effect sizes from small (Cohen’s f = 0.10), medium (f = 0.25), to large (f = 0.40) are considered to accommodate varying expected intervention effects, ensuring both robustness and generalizability of the findings [50]. Sample size calculations were conducted for the health outcomes (ACT and PFT) and environmental outcomes (IAQ and mold measurements). Required sample sizes were estimated based on expected effect sizes to achieve a statistical power >0.80 and adjusted for a 10% dropout rate. For monthly ACT surveys (n = 24) and monthly average low-cost IAQ measurements (n = 24), the required sample sizes ranged from 84 households for a small effect size (0.10) to 9 households for a large effect size (0.40). For PFT and mold measurements, the required sample sizes were estimated at 220 and 308 households, respectively, for detecting a small effect size (0.10); 40 and 53 households, respectively, for a medium effect size (0.25); and 18 and 26 households, respectively, for a large effect size (0.40). Although larger sample sizes were required to detect a small effect size (0.1) for PFT and mold, these estimates represent the sample sizes needed to detect very small changes. Further, the AIRVAC study was primarily designed to evaluate intervention effects on asthma outcomes and IAQ, for which the estimated sample sizes were within the planned recruitment range. Therefore, the final target sample size was set at 80 households, with an initial recruitment target of 88 households to account for potential dropout.

**Table 1 pone.0358221.t001:** Sample size calculations.

Effect Size (Cohen’s f for ANOVA)	Small			Medium			Large
	0.1	0.15	0.2	0.25	0.3	0.35	0.4

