**Mold Measurements (No. of measurements = 2, baseline & end-line)**							
Statistical Power	0.81	0.81	0.82	0.8	0.82	0.83	0.86
Sample Size Per Group	70	32	19	12	9	7	6
Total Sample Size	280	128	76	48	36	28	24
Total Sample Size (adjusted for 10% dropout)	**308**	141	84	**53**	40	31	**26**

Sample sizes were calculated based on repeated measures ANOVA (α = 0.05, power = 0.80) and expected effect sizes, with adjustment for a 10% dropout rate.

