The primary analyses will follow the intention-to-treat (ITT) principle, including all randomized households analyzed according to their assigned intervention group, to evaluate the effects of ERVs and portable HEPA air cleaners on IAQ, mold reduction, and asthma-related health outcomes by comparing the intervention and control (sham) groups using repeated measures analysis of variance (ANOVA) with a within-between interaction. Pairwise comparisons will be conducted between each intervention and control group (Group 1 vs. Group 2, Group 3 vs. Group 4) and between intervention groups (Group 1 vs. Group 3), using Tukey’s Honest Significant Difference (HSD) test to adjust for multiple comparisons. Repeated monthly ACT scores will be analyzed using multivariate mixed-effects models to account for within-subject correlations over time. Per-protocol (PP) analyses will be conducted as sensitivity analyses and will include only households that adequately adhered to the assigned intervention protocol. Intervention adherence will be assessed using plug load logger data for both ERV and air cleaner units, including device operation status and operating duration [52]. Additionally, subgroup analyses will be conducted to explore whether intervention effects differ by demographic and socioeconomic characteristics, baseline asthma severity, and baseline IAQ.

For secondary analyses, multivariate linear and logistic regression models will examine associations among housing characteristics, occupant behaviors, indoor environmental exposures (e.g., air pollutants and mold), and asthma-related health outcomes. Housing characteristics will be considered as potential covariates or confounders, when applicable, based on biological plausibility and statistical considerations. Prior to multivariable modeling, correlations among environmental exposure variables (e.g., PM, NO_2_, VOCs, and mold indices) will be evaluated using Pearson or Spearman correlation coefficients, depending on data distribution. Variance inflation factors (VIFs) will also be calculated to assess multicollinearity among predictors. Highly correlated exposures will not be included simultaneously in the same model to minimize multicollinearity, overfitting, and unstable estimates.

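### The stated primary comparison of indoor air quality and mold names no outdoor term, although matching outdoor levels are to be measured; this costs precision, most of all for spore-trap counts

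*Protocol article*

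**What the plan says.** The section on data management and statistical analysis gives the primary intention-to-treat analysis of air quality, mold and health as "comparing the intervention and control (sham) groups using repeated measures analysis of variance (ANOVA) with a within-between interaction". The section on power calculations sizes the trial "for a repeated measures ANOVA with a within-between interaction". Neither place names an outdoor term.

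The section on environmental exposure assessments plans the outdoor data. It states that "low-cost sensors will continuously collect indoor and outdoor air quality data over the two-year study period". The low-cost units carry PM, VOC and NO2 sensors, and 160 are to be built. For mold, "Indoor and outdoor air samples will be collected using an Air-O-Cell sampling cassette", with sampling at V1 and V4.

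Three other statements bear on the point:
- The study design section says that seasonal variation will be handled in longitudinal analyses with covariates related to time.
- The analysis section says, in its missing-data text, that mixed-effects models for repeated measures will account for within-subject correlation. Later it assigns mixed models by name to the monthly ACT scores.
- The analysis section says that the calibrated sensor data, which include the outdoor data, will feed all the analyses. It does not say how. The secondary models list indoor exposures only.

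**The concern.** Outdoor pollution and spores enter homes, so they add to the variation in indoor levels between months and visits. The assigned device has practically no influence on the outdoor level. Adjusting for it therefore removes noise without removing treatment effect.

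An effect of study occasion does not do this job. Recruitment runs from September 2025 to September 2026, so the same study month falls in different calendar months in different homes. The pre-intervention period is capped at one year but not fixed, and data collection is due to end by February 2028. A home recruited in September 2025 can have V1 and V4 almost two years apart, in similar seasons. A home recruited in September 2026 has at most 17 months (September 2026 to February 2028), so its V1 and V4 can fall in different seasons. The outdoor change between the two visits then differs between homes and goes into the error term.

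At stake is the precision of the air quality and spore-trap comparisons. Spore-trap counts are the most exposed, because a single sample on each side cannot average outdoor swings away.

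**Working it through.** **Inputs from the protocol article.** Four arms; α = 0.05; target power 0.80; 80 households; 24 occasions for ACT and monthly air quality and 2 for mold; Cohen's f from 0.10 to 0.40.

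**Inputs assumed.** Correlation among repeated measures ρ = 0.5 and sphericity ε = 1 (neither is stated). R², the share of within-home error variance (for two occasions, of the before-after change) explained by outdoor level, is not given; 0.1 to 0.5 is used as a range.

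**Step 1: reproduce Table 1.** For the within-between interaction with k groups, m occasions and N homes:

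λ = f²·N·m/(1 − ρ), df1 = (k − 1)(m − 1), df2 = (N − k)(m − 1), power from the noncentral F.

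- Air quality, f = 0.10, N = 76: λ = 0.01 × 76 × 24/0.5 = 36.48, df 69 and 1656, power 0.815 (stated 0.82).
- Mold, f = 0.10, N = 280: λ = 0.01 × 280 × 2/0.5 = 11.2, df 3 and 276, power 0.806 (stated 0.81).

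Every per-group size in Table 1 is reproduced. Of the 21 stated powers, 20 agree; the exception is 24 occasions at f = 0.40 (stated 0.92, computed 0.898). The sample sizes are thus those of a model without covariates, and take no credit for outdoor adjustment.

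**Step 2: a contrast planned at 80% power.** Adjustment divides the error variance by 1/(1 − R²):

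power = Φ(2.802/√(1 − R²) − 1.96); equivalent extra homes = 1/(1 − R²) − 1.

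| R² | Power | Equivalent extra homes |
|---|---|---|
| 0.1 | 0.840 | 11% |
| 0.2 | 0.880 | 25% |
| 0.3 | 0.918 | 43% |
| 0.5 | 0.977 | 100% |

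**Step 3: the trial's own model at N = 80**, with λ replaced by λ/(1 − R²). For mold at f = 0.15, λ = 0.0225 × 80 × 2/0.5 = 7.2 before adjustment.

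| R² | Air quality, f = 0.10: power | Mold, f = 0.15: power | Mold: smallest f with 80% power |
|---|---|---|---|
| 0 | 0.84 | 0.58 | 0.189 |
| 0.1 | 0.89 | 0.63 | 0.180 |
| 0.2 | 0.94 | 0.69 | 0.169 |
| 0.3 | 0.97 | 0.75 | 0.158 |
| 0.5 | 0.998 | 0.89 | 0.134 |

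The mold columns apply to spore-trap counts only.

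**Step 4: bias or precision?** An illustrative simulation used 20 against 20 homes, 12 months before and 12 after, entry staggered over 12 months, a true effect of −0.4, and 400 runs per setting with assumed variances. Mean estimates lay between −0.397 and −0.409 unadjusted and between −0.401 and −0.405 adjusted, so neither is biased. Across four settings of outdoor variation, unadjusted power was 0.82, 0.75, 0.61 and 0.53, while adjusted power stayed at 0.84 to 0.86. The outdoor variances are invented and the calendar-month swings were random, not a yearly cycle. The run shows the direction of the effect, not its size in this trial.

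**The case against.** **This is silence in a condensed article.** The methods refer to a prespecified analysis plan that is not shown, and covariate lists are commonly left to it. This stands in part. A reader might infer that the outdoor data will be ignored, or that they cannot enter the analysis. The documents support neither: nothing excludes them, mixed models are mentioned, and the calibrated data are to be used throughout. What remains is that the article does name a primary model, sizes the trial on it, and gives outdoor levels no role in the treatment comparison.

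**Season is already covered.** Time-related covariates may absorb shared seasonal swings, and over a full year before and after much of the season averages out. This also stands in part. Such covariates do not capture outdoor levels specific to a home or a day, the pre-intervention period may be shorter than a year, and a spore trap is one sample per visit.

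**Outdoor counterparts exist for only some outcomes.** This stands. NO, CO, O3 and formaldehyde are described only for research-grade monitors beside the indoor sensors. Surface swabs and dust DNA have no outdoor match. These outcomes are outside the point. Also, 160 units make pairs for 80 homes, while about 88 are to be recruited.

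**The gain is assumed.** This stands. No indoor-outdoor correlation is given, and the introduction stresses indoor combustion sources, so R² may be low for some pollutants. For air quality, power is already about 0.84 at f = 0.10 with 80 homes under the planning assumptions. That figure itself leans on the unstated correlation: with ρ = 0.3, the 76 homes would give 0.61.

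**One common outdoor slope is not enough.** This stands. Active ERVs supply outdoor air, while sham ERVs recirculate with the intake closed, so the slope may differ by arm.

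**Conclusion.** The point holds as a matter of precision. The named primary model for air quality and mold has no outdoor term, although the trial plans matching outdoor measurements of PM, NO2, VOCs and airborne spores. With staggered entry and a pre-intervention period of varying length, outdoor variation between homes and visits stays in the error.

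The size cannot be computed from the documents. Under an assumed R² of 0.1 to 0.5, 80% power would become about 84% to 98%. Spore-trap counts stand to gain most: under ρ = 0.5 and ε = 1, power at f = 0.15 with 80 homes is 0.58 without adjustment and 0.63 to 0.89 with it. The gain may be small for pollutants with mainly indoor sources.

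A reader might also infer that the unadjusted comparison is biased or invalid. It is not: outdoor level is unrelated to randomised assignment, and the simulation showed no bias.

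**What to change.** Before the analysis plan is finalised, specify the following for indoor PM, NO2, VOCs and spore-trap counts only:

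- A mixed model with arm, period, arm-by-period and the concurrent outdoor level of the same measure (log scale, centred) as a time-varying covariate. For spore traps this is the outdoor sample of the same visit.
- Consideration of a centred outdoor-by-arm term, with the arm effect reported at the mean outdoor level.
- The unadjusted analysis as a sensitivity analysis.

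The change is to analysis wording. The outdoor measurements are already planned and, by the article's account, data collection has not begun, so the model can still be prespecified. There are small costs. Missing outdoor readings must be imputed, including for any homes beyond the 80 that the sensors can pair. Noise in the outdoor sensors reduces the gain. An outdoor-by-arm term uses a few degrees of freedom.

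### For the monthly outcomes, the stated ANOVA interaction (69 df as sized) does not isolate the pre-to-post change versus sham, and ACT has two methods with no order of precedence

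*Protocol article*

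**What the plan says.** In the protocol article, Data management and statistical analysis plan, the primary intention-to-treat comparison covers IAQ, mold and asthma outcomes and is made "using repeated measures analysis of variance (ANOVA) with a within-between interaction". Group 1 vs 2, Group 3 vs 4 and Group 1 vs 3 are then compared with Tukey's "Honest Significant Difference (HSD) test to adjust for multiple comparisons". The next sentence says: "Repeated monthly ACT scores will be analyzed using multivariate mixed-effects models".

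The Power calculations section sizes the trial "for a repeated measures ANOVA with a within-between interaction". The number of repeated measures is 24 for the monthly outcomes: "For monthly ACT surveys (n = 24) and monthly average low-cost IAQ measurements (n = 24". It is 4 for pulmonary function and 2 for mold (Table 1).

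Under Objectives and hypotheses, the active arms are expected to improve from the pre- to the post-intervention period and the control arms are not. The article defines no before/after period factor and no difference-in-change contrast. It does not say which means Tukey HSD compares.

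**The concern.** With 24 months and four arms, the interaction is significant for any difference in monthly pattern among any arms. That includes differences confined to pre-installation months and differences between the two sham arms. A rejection therefore does not answer the stated question, and power is spread over 69 degrees of freedom when the effect of interest is one step at installation.

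Three further matters follow:
- The F test relies on sphericity, which consecutive months are unlikely to satisfy.
- The pairwise step is open to a reading that averages the effect over a year in which no device was running.
- ACT, a primary outcome, can be analysed in two ways, and the power table covers only one of them.

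At stake is whether the trial's main result on the outcomes it was chiefly sized for can be read as an effect of the devices.

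**Working it through.** **Inputs from the article.** k = 4 arms; m = 24 monthly values; f = 0.10; N = 76 (19 per arm) with stated power 0.82; alpha 0.05; target 80 homes (20 per arm if equal). **Assumed, because not stated:** correlation rho = 0.5 and epsilon = 1. These values reproduce all 21 per-group sizes in Table 1.

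**1. Reproducing the stated power.**
- df1 = (4 − 1)(24 − 1) = 69; df2 = (76 − 4) × 23 = 1656.
- lambda = f² × N × m × epsilon / (1 − rho) = 0.01 × 76 × 24 / 0.5 = 36.5.
- Power = 0.815, against 0.82 stated. The ACT/IAQ rows are therefore the 24-level test with sphericity assumed. At N = 80 the power is 0.84.

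**2. What f = 0.10 means here.** Suppose both active arms shift by delta in the 12 months after installation. Each interaction term is then ± delta/4 (for example delta − delta/2 − delta/2 + delta/4). So f = 0.25 delta/SD, and f = 0.10 is a step of 0.4 SD.

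**3. Group 1 vs 2, 20 homes per arm, 12 + 12 months, rho = 0.5.**
- Change contrast: SE = sqrt(2 × 0.5 × (1/12 + 1/12)/20) = 0.091 SD; 0.4/0.091 = 4.4.
- Arm means over all months: variance 0.5 + 0.5/24 = 0.521; SE = sqrt(2 × 0.521/20) = 0.228 SD. The effect is halved to 0.2, so 0.2/0.228 = 0.88.
- Critical values at 76 df: Tukey over six pairs 2.63; Bonferroni over three 2.45.
- Power of the change contrast: 0.96 (Tukey) or 0.97 (Bonferroni). Power of Tukey on all-month means: about 0.05.

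**4. Level and power when months are autocorrelated.** Simulation used 4 × 20 homes × 24 months, with 3000 null runs. All correlation structures are assumptions.
- Uncorrected 69-df test under pure AR(1): 0.066 at lag-1 0.3, 0.090 at 0.5, 0.136 at 0.7, 0.196 at 0.9. Intermediate structures give about 7–12%.
- Greenhouse-Geisser correction: 0.028–0.050.
- 3-df arm-by-period test: 0.043–0.056 throughout.
- Cost of correcting, by the formula in step 1 at N = 76: power 0.72 at epsilon 0.75, 0.57 at 0.5, 0.42 at 0.3.
- For the 0.4 SD step with a random intercept (half the variance) plus AR(1) 0.5 (epsilon 0.63; 1500 runs): corrected omnibus 0.65, 3-df change test 0.92, Group 1 vs 2 change contrast 0.80 before multiplicity adjustment.

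**5. Specificity.** A 12-month seasonal cycle of 0.5 SD amplitude in one arm only, with essentially no pre/post difference, was rejected in 99.9% of runs by the omnibus and in 6% by the change test. This illustrates what the omnibus responds to. It is not a forecast.

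**6. Calendar.** Recruitment runs to September 2026 and data collection is expected to end by February 2028, about 17 months later. A last entrant with 12 post-intervention months has about 5 before. The pre-period is itself described as lasting up to one year. A 24-level month factor will therefore be incomplete for some homes and will not line up with installation.

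**The case against.** The article does not list the levels of the time factor in the analysis itself. The 24 levels come from the sizing, so 69 df is an inference for the analysis. It is a strong inference for sensor IAQ and a weaker one for ACT, because the specific mixed-model sentence can be read as the rule for monthly ACT. The Study design section also promises time-related covariates for season. All of this stands, and it narrows the point to the monthly outcomes.

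Four stronger readings might be inferred and are not supported:
- **That the primary test fails to hold 5%.** This requires an uncorrected F test. The article is silent on correction, which an analysis plan commonly settles, and Greenhouse-Geisser restores the level.
- **That Tukey HSD is an error or will miss the effect.** The low power arises only on all-month means, which the text does not specify. On change contrasts Tukey loses about one point to Bonferroni over three (0.96 against 0.97).
- **That the interaction is wrong for every outcome.** Mold is measured twice, at V1 and V4, so its 3-df interaction is the pre-to-post change by arm, and sphericity does not arise. Visit-based outcomes with four measurements give 9 df.
- **That a false device claim is likely.** Active and sham are randomised within device type, so differences in monthly pattern between them before installation are chance and are covered by a valid test's level.

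The objection does not remove the mismatch between the test named and sized for the monthly outcomes and the stated hypothesis, nor the unresolved choice of method for ACT. These are things the article states, not details it leaves out.

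**Conclusion.** The point holds for monthly IAQ, and for monthly ACT so far as the ANOVA applies to it. The analysis section names the interaction as primary, the power section sizes it as a 69-df test under sphericity, and that test does not isolate post-versus-pre improvement against sham. In the article's own f = 0.10 case, under rho = 0.5 and sphericity, the omnibus has 0.84 and the direct contrast 0.96–0.97.

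The remaining effects are conditional. If the F test is uncorrected, the level is about 7–12% under moderate assumed autocorrelation, with a wider range shown above. If it is corrected, the stated 0.82 is not reached (about 0.57 at epsilon 0.5). If Tukey is applied to all-month means, pairwise power is about 0.05.

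ACT has two methods with no stated precedence, and the power table does not size the mixed model. The contrast's own power also depends on the correlation (0.80 unadjusted in the autocorrelated case), so the 0.96 should not be carried over as the new power claim.

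**What to change.** - Name one primary model for each monthly outcome: a linear mixed model with arm × period (before/after installation), calendar month, and a stated autocorrelated or robust error structure. Say explicitly that this is the primary method for ACT.
- Make the difference in pre-to-post change the tested quantity for Group 1 vs 2, 3 vs 4 and 1 vs 3, and apply the multiplicity adjustment to these contrasts. Holm over three is slightly more efficient; Tukey on the same contrasts is acceptable.
- Restate the ACT/IAQ rows of Table 1 on that contrast, giving the assumed correlation structure, a range for it, and the expected number of pre-installation months.
- Keep the two-measurement interaction for mold.

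The cost is analysis wording and a rerun of part of the power table. No new data are needed, and the article reports that data collection has not begun.
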